### Organization and statistical treatment of data

The data will be tabulated and treated with the aid of SPSS 12.0 for Windows. Descriptive analysis of the data will be performed. Either the chi-squared test or Fisher’s exact test will be used to determine associations among the categorical variables. Student’s *t*-test and analysis of variance (ANOVA) will be used to compare mean colorimetric data. Pearson’s correlation coefficients will be calculated to determine the strength of correlations among the continuous variables. The level of significance will be set at 95% (*P* <0.05).

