**Table 1 Tab1:** **Summary of experimental conditions**

Group	Presence or absence of change in tooth color	Application site	Treatment
1	Presence	Maxillary and mandibular anterior teeth	Placebo gel without hydrogen peroxide - Formula e Açao – Sao Paulo/SP
			- without activating source
2	Presence	Maxillary and mandibular anterior teeth	6.0% hydrogen peroxide –White Class with Calcium, FGM – Joenville/SC
			- without activating source
3	Presence	Maxillary and mandibular anterior teeth	7.5% hydrogen peroxide –White Class with Calcium – FGM – Joenville/SC
			- without activating source
4	Presence	Maxillary and mandibular anterior teeth	7.5% hydrogen peroxide – Oral-B 3D White, Oral-B - EUA
			- without activating source

For each group, 16 individuals enrolled at the Dental Clinic of the University Nove de Julho will be selected. After receiving all necessary information regarding the study, including the procedures and possible risks, the volunteers who agree to participate and their respective guardians will sign a statement of informed consent.

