### Evaluations

Evaluations of dental sensitivity, discoloration and satisfaction with the whitening will be carried out for all groups at the following times: pre-treatment period (T1), immediately following the first treatment period (T2), after 7 days (T3), after 30 days (T4), after 6 months (T5), after 12 months (T6), after 24 months (T7) and after 48 months (T8).

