### Colorimetric evaluation

The tooth color of all participants will be evaluated before and after the whitening procedures. Color readings of the vestibular region of the maxillary and mandibular anterior teeth will be performed by a previously trained examiner blinded to the allocation of the volunteers to the different groups. A digital spectrophotometer will be used for the colorimetric evaluation.

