### Calculation of sample size

Considering a difference of 2.8 in *W*, 95% power, 5% error and standard deviation of 2.1 based on data from the literature [15], a minimum of 16 participants are needed for each group (see Table 1), to which 15% will be added to compensate for possible losses, totaling 19 volunteers per group. This calculation was made using the STATISTICA program.

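### Tooth colour is to be compared by plain t-test and ANOVA, with the response left open and no adjustment for the T1 reading that every participant has

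*Protocol article*

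**What the plan says.** The section on organization and statistical treatment of data gives the colour analysis in one sentence: Student's t-test and ANOVA "will be used to compare mean colorimetric data". It mentions no covariate, change score or repeated-measures model.

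The Evaluations section lists eight time points for all groups, the first (T1) before treatment. The Colorimetric evaluation section adds: "The tooth color of all participants will be evaluated before and after the whitening procedures". The abstract and the specific objectives describe the outcome as change in colour. The inclusion criteria restrict entry to teeth whose starting colour matches shade A2.

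The sample size section opens "Considering a difference of 2.8 in" W and continues with "95% power, 5% error and standard deviation of 2.1 based on data from the literature". It concludes that "a minimum of 16 participants are needed for each group", "to which 15% will be added to compensate for possible losses, totaling 19 volunteers per group". It does not say whether the 2.8 and the 2.1 refer to a post-treatment level or to a change from T1.

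**The concern.** A continuous baseline measurement of the outcome is planned for everyone, and the stated method makes no declared use of it. Two things follow.

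- **The response is not fixed.** The means compared could be post-treatment readings or changes from T1. These are different analyses with different variances, and which is the more precise depends on a correlation that the article does not give.
- **Precision is given up under either reading.** Post-treatment means ignore T1, so chance differences in starting colour add noise to the comparison. Change scores subtract the whole baseline value, which over-corrects when the correlation is below 1 and the variances are equal. Adjusting for T1 as a covariate avoids both.

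At stake is the width of the confidence intervals in a four-arm trial planned on 16 participants per group.

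**Working it through.** **Inputs from the article.** Difference 2.8 W, SD 2.1, power 95%, error 5%, 16 per group before losses (Calculation of sample size); four groups (Table 1).

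**Assumptions.** Correlation r between T1 and follow-up colour: not given, so a range is shown. Equal variances σ² before and after treatment.

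**Step 1: the stated sample size.** For an unadjusted two-sided comparison of two means, the normal approximation gives

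n = 2 × (1.960 + 1.645)² × (2.1/2.8)² = 2 × 13.0 × 0.5625 = 14.6, so 15 per group.

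The exact noncentral t calculation gives 16 per group, with power 95.4%. A one-sided test gives 13 and does not match. For losses, 16 × 1.15 = 18.4 and 16/0.85 = 18.8, and both round up to 19. The stated figures are therefore those of an unadjusted two-sided t-test, and the sizing takes no credit for baseline adjustment.

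**Step 2: variance under the three analyses.**

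- Post-treatment value: σ²
- Change from T1: 2σ²(1 − r)
- ANCOVA on T1: σ²(1 − r²)

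The ratio of ANCOVA to post-treatment values is 1 − r², a cut of r². The ratio of ANCOVA to change scores is (1 − r²)/[2(1 − r)] = (1 + r)/2, a cut of (1 − r)/2.

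| r | Cut against post-treatment means | Cut against change scores |
|---|---|---|
| 0.1 | 1% | 45% |
| 0.3 | 9% | 35% |
| 0.5 | 25% | 25% |
| 0.7 | 49% | 15% |

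Interval width scales with the square root of the variance. At r = 0.3, 0.5 and 0.7 the ratios to post-treatment means are √0.91 = 0.95, √0.75 = 0.87 and √0.51 = 0.71. The ratios to change scores are √0.65 = 0.81, √0.75 = 0.87 and √0.85 = 0.92.

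The two simple analyses are equally precise at r = 0.5, because 2(1 − 0.5) = 1. Below that the post-treatment value is the better of the two, and above it the change score is.

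**Step 3: power at 16 per group (normal approximation).** Unadjusted power is 96.5%. If 2.1 is the SD of the post-treatment value, ANCOVA gives 97.7% at r = 0.3, 99.2% at 0.5 and above 99.9% at 0.7. If 2.1 is the SD of change, it gives 99.7%, 99.2% and 98.3%.

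**Step 4: cost.** With 4 × 16 = 64 participants, a one-way ANOVA leaves 64 − 4 = 60 residual degrees of freedom and ANCOVA leaves 59. One in 60 is 1.7%, so at r = 0.1 the 1% saving against post-treatment means is roughly cancelled. At r = 0.3 and above it clearly exceeds the cost.

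**The case against.** **The compared means may already be changes from T1.** This stands. The abstract and objectives speak of change in colour, and ANOVA could also mean a repeated-measures analysis over the visits. A reader might infer that raw post-treatment means are compared and T1 is discarded, but the article does not establish that. The precision point survives because change scores are also less precise than ANCOVA whenever r is below 1 and the variances are equal.

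**The unadjusted test is valid.** This stands too. A reader might take chance baseline imbalance to mean bias. Under random allocation the comparison is unbiased, and its standard error already reflects such imbalance. The plan also reaches its 95% power without adjustment, though for a single two-group comparison with 16 evaluable per group.

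**The size of the imbalance cannot be derived.** One might use the planning SD as the baseline SD: 1.96 × 2.1 × √(2/16) = 1.46 W, about half the 2.8 target. The article does not support this. It does not say whether 2.1 belongs to a level or a change, and the A2 rule probably makes the baseline spread smaller. The same rule may lower r, which shrinks the gain against post-treatment means but enlarges it against change scores.

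**An article condenses.** Model terms are often left to a fuller document, and silence on a covariate would not by itself be a finding. Here, however, the article does name its colour tests, and neither is a baseline-adjusted model.

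**Adjustment should not be carried over without thought.** The section on the placebo gel says that group 1 receives 6.0% hydrogen peroxide 30 days after starting, so later contrasts with group 1 are not placebo contrasts, adjusted or not. The quoted sentence concerns colour only and gives no basis for extending the point to the sensitivity scale.

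**Conclusion.** The point holds as one of efficiency and of an unstated response. The colour analysis as written is valid but less precise than the planned data allow. ANCOVA on T1 would cut residual variance by 9% to 49% if post-treatment values are meant, or by 35% to 15% if changes are meant, as r runs from 0.3 to 0.7. Against whichever simple analysis is the better at each r, the saving is 9%, 25% and 15% at r = 0.3, 0.5 and 0.7.

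These figures rest on equal variances before and after treatment and on an r that the article does not give. If r is as low as 0.1 and post-treatment values are compared, there is practically nothing to gain. The change is worth making because it costs almost nothing. It is not needed to rescue the trial's validity or its planned power.

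**What to change.** In the section on organization and statistical treatment of data:

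1. State the colour response (which index, at which visit) and say in the sample size section whether the 2.8 and 2.1 refer to a level or to a change from T1.
2. Replace the plain t-test and ANOVA for colour with ANCOVA, with treatment group as factor and the participant's T1 value of the same index as covariate. Report adjusted group differences with 95% confidence intervals.
3. Limit contrasts that use group 1 as placebo to readings taken before that group receives peroxide. T5 to T8 fall after that point. T4 is nominally at 30 days, so it qualifies only if the reading precedes the first peroxide application.

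The cost is a few sentences and one residual degree of freedom (60 to 59 with 16 per group). No new data are needed, since T1 colour is already scheduled for everyone. The Trial status section describes the study as still recruiting, so at that stage the change could be specified before any baseline imbalance or outcome comparison could influence it.

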## Discussion

Tooth whitening can be performed in a dentist’s office or with the use of a home kit [3]. At-home whitening should be supervised by a dental professional and consists of the application of different concentrations of a peroxide gel (carbamide or hydrogen) to the teeth with the aid of personalized molds [9]. A number of publications have attested to the efficacy and biological safety of the at-home method [2, 10, 16]. Since the first proposal for home tooth whitening by Haywood and Heymann [9], both *in vitro* and *in situ* studies have demonstrated that whitening does not harm dental tissues and allows surprising esthetic results when properly employed [1, 17].

It is important to understand the action mechanism of the whitening agent and possible chemical interactions with dental tissues to minimize undesirable effects, such as tooth sensitivity. Hydrogen peroxide (H_2_O_2_) is the main whitening agent employed. It is a thermally unstable free radical with a low molecular weight, which penetrates the enamel and dentin through diffusion [18]. Complex molecules of organic pigments in the tissues are broken down into simpler hydrophilic molecules through an oxidation-reduction reaction by the action of perhydroxyl ions originating from the degradation of H_2_O_2_
[1]. These simpler molecules are easily removed from the dental tissue when in contact with water, thereby providing the desired whitening effect [5, 6, 16–20]. This is the action mechanism of peroxide in both the whitening process performed in the dentist’s office and the self-administered method performed in the comfort of the patient’s own home [1, 5, 6].

The concentration of the whitening agent and exposure time on the dental surfaces are important aspects to consider. Haywood and Heymann [9] proposed the home whitening of vital teeth with a 10% carbamide peroxide gel applied with the aid of molds. This protocol is still considered the gold standard for comparisons with novel methods. The main problems reported in studies involving different concentrations of carbamide peroxide (10 to 22%) are linked to the duration of use and contact between the gel and dental surfaces (an average of 6 hours, which is considered high by current standards) [1, 6, 19, 20] and the occurrence of gingival irritation and dental sensitivity during treatment [3].

Currently, carbamide peroxide has been replaced by hydrogen peroxide in molds at concentrations of 6 to 9.5%. With the aim of accelerating the home whitening process, H_2_O_2_ has become increasingly popular. The main advantage is the shorter application time (30 to 90 minutes), through the greater concentration of the product (10% carbamide peroxide leads to the formation of 3.5% H_2_O_2_) [18].

Most authors agree that whitening agents greatly improve a patient’s self-esteem [4-6,21]. The benefits of current whitening systems and the desires of consumers, fueled to some extent by the standards of beauty dictated by society [1], have stimulated the development of over-the-counter products sold in pharmacies and supermarkets without the need for a prescription or professional supervision [1, 10, 11]. These whitening products first appeared in the USA in 2000 as an alternative to dental staining treatment, with a lower cost in comparison to traditional treatment by dentists [10]. In the last 10 years, other over-the-counter whitening agents have been added, such as toothpastes, mouthwashes and chewing gum [10].

Despite the increase in over-the-counter whitening products, the small concentrations of peroxide lead one to have doubts regarding their true whitening potential [1, 11]. Moreover, the fact that these materials are employed without technical supervision causes discomfort in the scientific community, especially with regard to the abrasiveness of the components, possible morphological alterations and adverse effects on enamel exposed to more concentrated whitening agents [1, 10–13, 17]. Whitening strips and varnishes containing peroxide fall into this category of freely commercialized products without professional supervision, exposing individuals to allergic reactions, the ingestion of the whitening agent and dental sensitivity [12, 13]. Moreover, the lack of professional monitoring indicates a greater risk of the improper use of these products [11].

The safety, efficacy, long-term color stability and discomfort (dental sensitivity and gingival irritation) of over-the-counter whitening products need to be evaluated, quantified and described in the scientific literature.

## Trial status

The proposed study is currently in the recruitment phase and evaluation of tooth color.
